### Data collection

Information will be retrieved at the baseline visit, followed by 6-, 12-, 24-, and 36-months follow-up. Data collection will be done within the weight management centres, all of which are in ambulatory environments. A comprehensive questionnaire will be administered and includes information on demographics, child lifestyle behaviours, and readiness to change lifestyle habits. Many demographic and lifestyle-related questions were derived from the *Canadian Health Measures Survey*[34], which was done to enable comparisons between study participants and a nationally-representative sample of Canadians. Family eating patterns will be evaluated using a validated questionnaire [35] that has predicted changes in BMI z-score amongst children enrolled in a weight management program. To promote participant retention, site specific newsletters will be periodically mailed or emailed to families. This newsletter will serve as a reminder to participants of their upcoming appointment, will encourage families to contact CANPWR researchers if their contact information changes during the study and will update them on the study progress. If study participants stop attending the weight management program (either inactive or discharged), a research visit separate from clinical care will be arranged to enable data collection. When data are missing or if families discontinue study participation, whenever possible, data will be retrieved from children’s medical records to populate study-specific case report forms. Participating families will receive up to $100 in the form of gift cards as tokens of appreciation. All de-identified study data will be entered into a secure, encrypted *iDataFax* web-enabled software application for central storage at the Population Health Research Institute (PHRI) (McMaster University; Hamilton, ON). A complete list of the contributors to the CANPWR study including the Central Coordinating Site and the research staff at each site is listed in Additional file 1.

### Inter-site calibration procedures

Standardized, accurate, valid, reliable, and reproducible measures are fundamental to the success of CANPWR. Quality assurance and quality control procedures will be implemented, recorded, and monitored. Intra- and inter-site variation will be evaluated and reported as outlined below. CANPWR quality assurance processes have begun with harmonization and review of the methods applied at each site for collection of outcome variables and determinants. Furthermore, training in completion of data collection forms and monitoring of completion of questionnaires will occur at each site and update courses will be offered as required. For laboratory measures, participation in accepted international quality assurance programs (e.g., College of American Pathologists) will be assured and monitored. Quality control processes are the operational techniques and activities used to fulfill requirements for quality. For physical measures, duplicate measures will be taken at defined intervals at each site to evaluate duplicate measures both within and between staff. These will be centralized and monitored on a periodic basis. A central research coordinator will travel between sites to fulfill several purposes, including ensuring study binders are complete and secure, to review data completion procedures with the study teams, review the periodic duplicate measures recorded, review training and monitor data collection (assuring consistency obtained from chart) and evaluate consistency of measures between sites.

### Statistical analysis

The results of patient demographics and baseline outcome variables (both primary and secondary) will be summarized using descriptive summary measures, expressed as mean (standard deviation) or median (minimum-maximum) for continuous variables and number (percent) for categorical variables. We will use multi-level or hierarchical modeling to analyze the data to address the primary and secondary aims [36] to determine the relationship between outcomes and individual-, family-, and program-level characteristics (Table 1). We will report the results as the estimate of the measure of association—model coefficients for continuous outcomes, odds ratios (OR) for binary outcomes or hazard ratio (HR) for time-to-event outcomes, corresponding 95% confidence intervals, and associated p-values. We will report p-values to three decimal places with p-values less than 0.001 reported as p < 0.001. All statistical tests will be performed using two-sided tests at the 0.05 level of significance. The Bonferroni method will be used to adjust the level of significance for testing for secondary outcomes to keep the overall level at α = 0.05. We will assess colinearity using the variance inflation factor (VIF) which measures the extent to which the variance of the model coefficients will be inflated. We will consider variables with VIF > 10 colinear and we will exclude them from the analysis [37]. We will perform all analyses using Statistical Analysis System (*SAS*) *version 9.2* (Cary, NC, USA).

Sensitivity analyses will be performed to assess the robustness of the results. First, there is likely to be missing data that will likely increase with time. We will use multiple imputations to handle missing data [38]. Second, there is likely to be high inter-correlations among outcomes. We will use a multivariate analysis of covariance (MANCOVA) approach to analyze all outcomes simultaneously. This method accounts for possible correlations among all outcomes and provides for a global assessment of the impact of each predictor variable with an indication of where differences exist. Third, we will use generalized estimating equations (GEE) assuming an auto-regressive correlation structure to account for possible serial correlation of measurements within a patient overtime [39]. Unlike ordinary linear regression, GEE allows accounting for possible serial correlation of outcomes within a patient over time.

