### Statistical power

Given a sample size of 1,600 and 41 variables or determinants to be included, the ratio of participants to variables is 39:1. Previous studies have shown that a fitted regression model is likely to be reliable and stable when the number of independent predictors is less than the total sample size divided by 20 [40]. Considering 40%, 25% or 15% dropout (n = 960, 1,200, 1,360 respectively), a two-sided test with significant level α = 0.05/4 = 0.0125 gives 90% power to detect a small R-square 0.0313 -0.0442 for 41 determinants. Thus, we have high power to test the effects of the described variables. For secondary hypothesis one (Table 1), we intend to examine three additional outcomes. To account for multiple hypothesis testing two-tailed α = 0.0125, we will continue to have power exceeding 90% to examine the influence of the determinants on the outcome at one year. For secondary hypothesis two, we intend to examine the determinants for sustainability of weight loss. To do so, we will examine the determinants for maintenance or decline of BMI z-score from year one to year two. If we conservatively estimate that at least 30% will have an increase in BMI z-score over that time period, we have 90% power to detect a variable that will increase this by 1.3 fold – and this is true even if we have 40% drop out from our study. Similarly, if the proportion of participants whose BMI z-score increases from year one to year two is higher, our power would be > 90%. Findings from several published trials suggest these assumptions are appropriate [21,41]. For secondary hypothesis three, we will examine the determinants of program drop out within one year of enrollment. We are sufficiently powered to detect an OR of 1.2 if 25% or more of those who commence a program drop out, and to detect an OR of 1.3 if only 15% drop out of the program.

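### Secondary outcomes are adjusted by single-step Bonferroni; Holm's step-down procedure gives the same overall 0.05 control and never rejects less, a minor but free gain in power

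*Protocol article*

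**What the plan says.** The Statistical analysis section of the protocol article sets the general rule: "All statistical tests will be performed using two-sided tests at the 0.05 level of significance". For the secondary outcomes it adds: "The Bonferroni method will be used to adjust the level of significance for testing for secondary outcomes", with the aim of holding the overall level at 0.05.

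The Statistical power section shows how the adjustment is meant to work. It takes "a two-sided test with significant level α = 0.05/4 = 0.0125" and says that this "gives 90% power to detect a small R-square 0.0313 -0.0442 for 41 determinants". It then says: "For secondary hypothesis one (Table 1), we intend to examine three additional outcomes". The divisor of four therefore reads most naturally as the primary outcome plus three more. A single fixed level is used throughout, and no step-down rule is mentioned.

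Two other statements in the Statistical analysis section matter here. The plan expects that "there is likely to be high inter-correlations among outcomes". It also promises 95% confidence intervals with the estimates and does not say that they are adjusted for multiplicity.

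**The concern.** Under single-step Bonferroni every outcome must clear 0.0125, however many of the others have already been established. Holm's procedure starts at the same 0.0125 and relaxes the level for the remaining outcomes each time one is rejected. Its guarantee needs no assumption about correlation, so it covers the strongly correlated outcomes that the plan expects.

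At stake is a secondary outcome whose p-value lies above 0.0125 but below the Holm level it would face. It would be reported as not significant only because the less efficient of two equally valid procedures was named. The primary analysis, the sample size and the validity of the error control are not affected.

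**Working it through.** **Inputs from the protocol article.** Overall α = 0.05, two-sided (Statistical analysis). Divisor 4, 41 determinants, 90% power and R-square 0.0313 to 0.0442 (Statistical power). Sample sizes from "Considering 40%, 25% or 15% dropout (n = 960, 1,200, 1,360 respectively". No numerical correlation between outcomes is given, so 0 to 0.6 is assumed. How many of the effects are real is also unknown and is varied below.

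**Step 1: the plan's own figure.** 0.05/4 = 0.0125. For the overall F-test of R-square with 41 predictors, the degrees of freedom are 41 and n − 42 and the noncentrality is λ = n·R²/(1 − R²). The R-square detectable with 90% power at 0.0125 is:

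- n = 960: 0.0439
- n = 1,200: 0.0352
- n = 1,360: 0.0311

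The stated range is 0.0313 to 0.0442. Power at its end points is 90.3% in both cases (R² = 0.0442 with n = 960; R² = 0.0313 with n = 1,360). The plan's figure reproduces.

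**Step 2: the two procedures.** Order the four p-values from smallest to largest. Bonferroni compares each with 0.0125. Holm compares the j-th smallest with 0.05/(4 − j + 1), that is 0.0125, 0.0167, 0.025 and 0.05, and stops at the first failure.

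- *Never rejects less.* Every Holm level is at least 0.0125, so any p-value that passes Bonferroni, and all smaller ones, also pass Holm.
- *Same error control.* Suppose m₀ of the m = 4 null hypotheses are true and the first false rejection comes at step j. At most m − m₀ rejections came before it, so m − j + 1 ≥ m₀ and that p-value is at most 0.05/m₀. The chance that any of m₀ true nulls has such a p-value is at most m₀ × 0.05/m₀ = 0.05, whatever the correlation.

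**Step 3: effect of the Holm levels in the plan's own test.** At the stated R-square end points, power at 0.05/4, 0.05/3, 0.05/2 and 0.05 is 90.3%, 91.9%, 94.0% and 96.7%.

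**Step 4: simulation.** Four two-sided z-tests, 400,000 replicates, each real effect given 90% power at 0.0125. The table shows average power per real effect.

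| Real effects | Bonferroni | Holm, correlation 0 | Holm, correlation 0.5 |
|---|---|---|---|
| 4 of 4 | 90.0% | 96.0% | 94.9% |
| 2 of 4 | 90.0% | 91.6% | 91.4% |
| 1 of 4 | 90.0% | 90.1% | 90.1% |

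With three of four real, Holm gives 93–94% over correlations 0 to 0.6. Extending the other rows to 0.6 leaves them at about 95–96%, 91–92% and a gain of about 0.1 point or less.

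With all four real, the chance of establishing all four rises from 65.5% to 86.5% (correlation 0) or from 74.2% to 88.9% (correlation 0.5). If each effect has only 60% power under Bonferroni and all four are real, average power rises from 60.0% to 70.6% or 69.0%.

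Simulated family-wise error under Holm stayed below 0.05 in every setting with four outcomes. In no replicate did Bonferroni reject something that Holm did not.

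**The case against.** **Bonferroni is valid and nothing is contradicted.** This stands. It keeps the overall level as stated, and the power section carries it through consistently. A reader might infer that the plan is wrong or the study underpowered. The documents support neither reading.

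**The gain depends on many effects being real.** This also stands. A reader might infer that a lost finding is likely. Secondary hypothesis one expects the determinants to influence these measures generally, but the article gives no probability that several effects are real. With one real effect the gain is negligible, and with none there is no gain.

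**Power is already high.** This stands in part. At n = 960, an R-square of 0.05 has 95.1% power at 0.0125 and 98.6% at 0.05. At n = 1,360 it already has 99.75% at 0.0125. The gain therefore shrinks once effects exceed the minimum detectable size, and it grows for smaller ones.

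**Holm does not rescue every p-value between 0.0125 and 0.05.** Correct. With four tests, p = 0.04 is rejected only if it is the largest and the other three have been rejected. The accurate claim is that Holm rejects at least as much, not always more.

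**Changing one word is not enough.** This stands. Holm needs a closed list with one p-value per outcome, whereas each model has 41 determinants and reports coefficients with p-values. The divisor is four, while Table 1 and the Measurements section list more than three secondary outcomes. The family has to be explicit, but Holm is at least as powerful whatever its size.

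**Bonferroni has simple matching simultaneous intervals.** True, and Holm does not. As the plan names only 95% intervals, it does not use this advantage.

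**Conclusion.** The point holds as a minor, essentially free improvement. The plan names a valid procedure where another gives the same family-wise control at 0.05, under any dependence, and never rejects less.

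For four outcomes at 90% power each under Bonferroni, the gain in average power is about 5 to 6 percentage points if all four effects are real, 3 to 4 if three are, 1 to 2 if two are, and about 0.1 or less if one is. These sizes rest on assumed correlations of 0 to 0.6, equal effect sizes, and power at the design minimum. That Holm is never worse rests on none of these assumptions.

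**What to change.** In the Statistical analysis section, name Holm's step-down procedure in place of the Bonferroni method, at overall two-sided 0.05. State that it is applied to one overall p-value per outcome, namely the joint test of the determinants used in the power calculation, within the prespecified family that the Statistical power section divides for. List the outcomes in that family. Make the change before outcome data are examined.

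Keep the plain 95% confidence intervals. Keep the power statement at 0.0125 as a lower bound, because Holm's first level is that level and later ones are larger; nothing needs recalculating.

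The cost is a sentence or two of text and no additional participants or data. The only thing given up is Bonferroni's simple simultaneous intervals. If the investigators do want those, that would be a reason to keep Bonferroni, and the plan should say so.

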**Table 1 T1:** **Objectives**, **hypotheses**, **measures**, **and methods of analysis**

**Objective**	**Hypothesis**	**Outcome measure ****(C = ****Continuous; ****B = ****Binary)**	**Methods of analysis**
**Primary**	Change in BMI z-score will be influenced by child/youth, family, and program characteristics consistent with our theoretical model	BMI z-score (C)	Hierarchical/multilevel modeling
Document changes in anthropometric, lifestyle, behavioural, and obesity-related co-morbidities in children enrolled in Canadian pediatric weight management programs over a three-year period			
**Secondary**	Change in cardiometabolic health outcomes will be influenced by child/youth, family, and program characteristics consistent with our theoretical model	Systolic and diastolic blood pressure (C)	Hierarchical/multilevel modeling
1) Document changes in anthropometric, lifestyle, behavioural, and obesity-related co-morbidities in children enrolled in Canadian pediatric weight management programs over a three-year period;			
		Blood glucose (Fasting & 2 hr post glucose load) (C)	
		Total cholesterol/HDL-C ratio (C)	
		Triglyceride (C)	
		Fitness (C)	
		Quality of Life (C)	
		Lifestyle behaviours (C)	
2) Characterize the individual-, family-, and program-level determinants of change in anthropometric and obesity-related co-morbidities;	Individual-, family-, and program-level determinants will be identified that predict sustainability of change from years 1 – 3.	BMI z-score (C)	Hierarchical/multilevel modeling
3) Examine the individual-, family-, and program-level determinants of program attrition.	Individual-, family-, and program-level determinants will differentiate those who dropped out of the program	Drop out from the program between enrollment and 1 year (B)	Hierarchical/multilevel modeling
			Logistic regression
**Exploratory analyses**	We will identify interaction terms between some individual, family and program determinants	All outcomes	Hierarchical/multilevel modeling
Identify what works best for what groups of individuals or families			
**Sensitivity analyses**	As above	All outcomes	1) Analysis with multiple imputation
1) Imputation methods			
2) All outcomes analyzed simultaneously to account for correlation among them			2) MANCOVA
			3) GEE
3) Serial correlation of all outcomes over time			

*MANOVA*: multivariate analysis of covariance.

*GEE*: Generalized estimating equations.

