### Measurements

Health outcomes and purported determinants that are evidence-based and measured at each centre with methodologies that have been standardized and harmonized through the initial phase of CANPWR will be included. The primary outcome is change in BMI z-score (WHO definition). Secondary health outcomes include absolute BMI [33], waist circumference, hip circumference, cardiometabolic measures (blood pressure, glycemia (fasting and two-hour blood glucose), lipid profile (total cholesterol/high density lipoprotein cholesterol ratio, and triglyceride), liver enzymes (AST, ALT)), aerobic fitness and quality of life (Peds QL). The determinants to be evaluated for their influence on change of the primary and secondary outcomes include individual, family, and program characteristics. Characteristics of the *Individual* include demographic (e.g. age, sex, ethnicity, immigrant status), biological (e.g. BMI z-score at baseline, medical history including medication use and other health disorder(s)) and life style behaviours (e.g. dietary intake, family eating patterns, sedentary activity, sleep, readiness to change, nutrition and physical activity habits). *Family* characteristics include family health (e.g. parental weight status, family history of type 2 diabetes, coronary heart disease), socioeconomic status, family structure (e.g. number of people living in household), and readiness to change nutrition and physical activity behaviours at baseline. *Program* characteristics will include intervention modality (individual *vs* group-based care), parental participation, participant satisfaction with care, proportions of clinical time families spend with different disciplines, number of clinic hours attended, clinical status at time of study visit (active, inactive or discharged), and adherence to scheduled clinic visits (proportion of planned visits attended).

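### The VIF rule, as written, excludes every variable above 10 at once, so it can delete both members of a collinear pair where dropping one would be enough

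*Protocol article*

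**What the plan says.** The Statistical analysis section names the diagnostic, "We will assess colinearity using the variance inflation factor (VIF) which measures the extent to which the variance of the model coefficients will be inflated", and then the cut-off and the action, "We will consider variables with VIF > 10 colinear and we will exclude them from the analysis". It gives no order of removal, no recomputation after a removal, no member of a collinear group to be kept, and no limit on which models are screened.

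The rule acts on a large determinant set. The Statistical power section says: "Given a sample size of 1,600 and 41 variables or determinants to be included, the ratio of participants to variables is 39:1". Among the program characteristics, the Measurements section lists "proportions of clinical time families spend with different disciplines, number of clinic hours attended" and also "adherence to scheduled clinic visits (proportion of planned visits attended"). For the exploratory analyses, Table 1 says "We will identify interaction terms between some individual, family and program determinants", for all outcomes. The article does not say how the discipline proportions are coded or whether continuous variables are centred before products are formed.

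**The concern.** VIF describes how well one variable is predicted by the others, so a high value belongs to a relationship and not to one offending variable. In a two-variable relationship both variables carry the same VIF. A rule that excludes everything above the cut-off therefore removes both sides, when removing either one would bring the other back to an acceptable value.

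The primary hypothesis and all three secondary hypotheses concern the influence of determinants. If a collinear pair is deleted, the effect that the two share goes untested, and the remaining coefficients can be confounded by what was removed. Two planned features look exposed. The first is the discipline-time proportions, which bear on a question that the Background calls unanswered: how, and with whom, clinical hours are spent. The second is the interaction terms.

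**Working it through.** **The plan's own figure.** The VIF rule has no numerical result to reproduce. The one figure tied to the determinant set is the detectable R-square in the Statistical power section: 0.0313 to 0.0442 for 41 determinants, α = 0.05/4 = 0.0125, 90% power and n = 1,360 down to 960. A noncentral F calculation (41 and n − 42 degrees of freedom, λ = n·R²/(1 − R²)) gives 0.0311 at n = 1,360 and 0.0439 at n = 960, so the range reproduces. Nothing below disturbs it.

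**A collinear pair (no data assumption).** If two variables are related only to each other, each has VIF = 1/(1 − r²). This exceeds 10 when r² > 0.9, that is |r| > √0.9 = 0.9487.

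- r = 0.90: 1/(1 − 0.81) = 5.3 each; both stay.
- r = 0.95: 1/(1 − 0.9025) = 10.3 each; both are excluded.
- r = 0.97: 1/(1 − 0.9409) = 16.9 each; both are excluded. In simulated data (n = 1,600) both had VIF 17.0. Removing one and recomputing left the other at 1.0.

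**Larger sets.** Not every member need exceed 10. Twelve independent simulated variables plus their noisy sum gave VIFs of 2.0 to 2.2 for the twelve and 14.3 for the sum, so only the sum would go.

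**Discipline proportions (simulated; number of disciplines and distributions assumed).** If all shares are entered and sum to one, each is an exact function of the rest and its VIF is infinite.

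| Coding | VIFs of the shares | Result |
|---|---|---|
| Four shares, rounded to two decimals, plus two unrelated variables; rule as written | 580 to 613 | 2 of 6 variables kept, no share left |
| Same data, largest VIF removed, then recomputed | 1.4 to 1.5 | 5 of 6 kept, three shares left |
| One share left out as reference, most mixes | 1.0 to 3.4 | nothing removed |
| Two dominant and two very small disciplines, smallest as reference | 11.5 and 11.8 for the dominant two | both dominant shares removed |
| Same mix, a dominant discipline as reference | 1.0 to 1.1 | nothing removed |
| All four entered with error of SD 0.03, so that they no longer sum exactly to one | 7.1 to 7.9 | nothing removed |

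**Interaction terms (means and SDs assumed).** For a continuous variable with mean m and SD s, multiplied uncentred by an independent balanced binary factor, VIF is 1 + (m/s)² for the factor, 2 + (m/s)² for the product and 2 for the continuous variable.

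- Age, mean 11, SD 3: (11/3)² = 13.4, giving 14.4 and 15.4.
- Age, mean 11, SD 3.5: 9.9, giving 10.9 and 11.9.
- Age, mean 11, SD 4: 7.6, giving 8.6 and 9.6; nothing is removed.
- BMI z-score, mean 3, SD 0.7: 18.4, giving 19.4 and 20.4.
- BMI z-score, mean 2.5, SD 0.9: 7.7, giving 8.7 and 9.7; nothing is removed.

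For age (mean 11.5, SD 3.5) by BMI z-score (mean 3, SD 0.8), simulation gave 14.9 and 11.1 for the components and 25.4 for the product. With centring, the simulated age-by-BMI and age-by-sex models had VIFs of about 1.0 throughout. A product of two binary factors gave 2.0, 2.0 and 3.1 without centring.

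**The case against.** The strongest reply is that this is a condensed article. Order of removal, recomputation, reference category and centring are routine content of an analysis plan that is not shown. The sentence also cites a source that cannot be consulted here. For the coding of the proportions and of the products, this reply largely stands: the article is silent, and silence of that kind is no error. It does not dispose of the exclusion rule. The article states a threshold and an action, and an analysis plan that removed one variable at a time would be changing that sentence, not filling a gap.

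The second reply is that no real collinearity has been shown. That is correct: the article gives no correlations, and no pair of listed determinants is known to approach 0.95.

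The third concerns reach. A reader might infer that the rule removes every member of any collinear set, and that the discipline proportions and interaction terms will therefore disappear. The documents do not support this. The twelve-plus-sum example shows that larger sets can lose a single member. Nothing says that all proportions are entered together, and with an intercept an exact full set has no unique fit under any rule, so leaving one out is the natural coding. Nothing says that the exploratory product terms are screened or left uncentred. With plausible spreads the product VIFs fall on either side of 10: eligibility runs from 2 to 17 years, and ages spread evenly over that range would have an SD of about 4.3.

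**Conclusion.** The point holds in limited form. The stated rule, followed as written, excludes both members of any pair with |r| above 0.9487 although dropping one would suffice. That is worse than an equally simple alternative, in a study whose hypotheses are about determinants. This part rests only on the wording and on VIF = 1/(1 − r²).

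The discipline proportions and the interaction terms are conditional risks. The first requires all shares to be entered and to sum to one, or a poorly chosen reference in a very uneven mix. The second requires uncentred coding, application of the screen to the exploratory models, and a mean-to-SD ratio above about 2.8 for the product (2 + (m/s)² > 10) or above 3 for the binary factor. Whether any determinant would in fact be lost cannot be told from the article. No stated figure is wrong because of this rule. It is a wording change worth making before the models are fitted.

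**What to change.** Replace the exclusion sentence with a sequential rule. When any VIF exceeds 10, remove or combine one variable at a time, keep the member of the collinear group that was prespecified as the representative, recompute all VIFs, and stop when none exceeds 10.

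Add two points on coding:

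- Enter the discipline-time proportions with one discipline as reference, preferably one that takes a large share of the time, since a very small reference share can itself push VIFs above 10.
- Centre continuous determinants before forming products, or exempt product terms from the VIF screen.

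The cost is slightly more analysis work and the need to decide beforehand which variable is kept in each group likely to overlap, such as clinic hours and the proportion of planned visits attended. No new data are needed and the sample size does not change.
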